### Study cohort

The study population includes CYP with medical complexity aged 0 to 18 years, referred for care coordination, who meet the following criteria:

– A diagnosis expected to last at least 12 months– And if ≥ 6months of age, frequent use of health services within the last six-month period, defined as:Two or more ED presentations, ORHospital admission for seven days or more, ORTwo or more outpatient appointments.

A cohort of CYP meeting these criteria and referred for care coordination, their parents and guardians, and clinical and non-clinical staff involved in the planning and/or delivery of the RuralKidsGPS model of care, will all form a part of the study cohort.

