#### Impact Evaluation Analyses

Based on local data from the participating LHDs, we aim to recruit 400 children across the four LHDs. We will match each case by 20 controls, resulting in a total of 8,000 controls. This will provide 90% power to detect a 20% difference in the number of health service use occasions, including outpatient visits and hospital admissions between intervention and comparison groups. Having 400 cases will also provide the power of 90% to detect a within-group 20% decrease in the number of health service use occasions. This sample size will also allow us to detect a clinically important difference (4.36 points) for child health related quality of life in children post- vs pre-intervention change in the PedsQL4.0 Total Scale Score [9].

We will calculate rate of health service use (e.g. ED, hospital admissions and OP visits) in person-years for the intervention and comparison groups during the baseline (3 years prior to enrolment) and the intervention period (12 months after enrolment), respectively. To assess the effectiveness of this intervention, we will conduct multivariable Poisson (negative binomial if over-dispersion is present) regression analysis with intervention status (intervention versus comparison) as the main independent variable and the rate of health service use (ED, hospital admissions and OP visits, separately and combined) during the intervention period as the outcome variable.

To examine how health service use changes over time between intervention and comparison groups, we will analyse rates of health service use during baseline and intervention periods using mixed effect Poisson regression models, including the interaction term between intervention status and time (after RuralKidsGPS implementation versus before RuralKidsGPS). In all regression analyses, we will control for participant socio-demographics (e.g., age at enrolment, sex, Aboriginal and Torres Strait Islander status, socio-economic status) and clinical factors (e.g., type and severity of health conditions), and baseline rate of health service use. Considering potential clustering effect by site, we will use the generalised estimating equations (GEE) approach in the regression analysis.

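### Baseline service-use rate is set as a covariate in every regression, including the before/after model whose outcome already contains it

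*Protocol article*

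**What the plan says.** All of this is in the protocol article. Impact Evaluation Analyses describes two count models for service use.

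- **Post-period model.** The outcome is the rate in the intervention period only, with intervention status as the main predictor. The article uses this model to assess effectiveness.
- **Before/after model.** For change over time, "we will analyse rates of health service use during baseline and intervention periods using mixed effect Poisson regression models". The quantity of interest there is a group-by-period interaction, with period coded as before or after the service began.

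The covariate rule follows: "In all regression analyses, we will control for participant socio-demographics", then clinical factors, "and baseline rate of health service use". It exempts neither model and gives no scale for the rate. The paragraph ends by naming GEE for clustering by site, without saying which model this applies to.

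The periods are defined as "during the baseline (3 years prior to enrolment) and the intervention period (12 months after enrolment", and rates are per person-year. Study cohort admits children "aged 0 to 18 years" and applies the prior service-use criterion only from 6 months of age.

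**The concern.** Adjusting for the baseline rate is ordinary in the post-period model. In the before/after model the same quantity then stands on both sides, because baseline-period use is one of the two outcome rows per child.

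Two things could go wrong. First, the coefficient for group at baseline, which should show how far the non-randomised groups differed beforehand, is estimated after conditioning on the outcome it describes. Second, the group-by-time interaction could be disturbed. A child-level covariate cancels exactly from that contrast when every child has the same ratio of follow-up to baseline time. Children under 3 cannot have 3 years of baseline, and infants may have only weeks, so exact cancellation is not assured.

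**Working it through.** **Stated figure nearby.** The section claims 90% power for a 20% difference with 400 cases and 8,000 controls. It gives no mean count or dispersion, so the figure can be neither reproduced nor refuted. It is not at issue here.

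**Why the interaction usually survives.** Let child *i* in group *g* have exposure *e*<sub>i0</sub> before and *e*<sub>i1</sub> after, and let *X*<sub>i</sub> be the baseline rate. In a Poisson model with a child intercept, conditioning on the child's total count gives a post-period share with

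logit *p*<sub>i</sub> = log(*e*<sub>i1</sub>/*e*<sub>i0</sub>) + τ + δ*G*<sub>i</sub>.

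The child intercept, the group main effect and γ*X*<sub>i</sub> all drop out. With equal exposure ratios the random-intercept estimate of δ is therefore the same with or without *X*. With unequal ratios a little information on δ leaks in from the totals.

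In an independence GEE, observed and fitted totals agree in each group-by-period cell, so

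δ̂ = log{ [(Y<sub>11</sub>/W<sub>11</sub>)/(Y<sub>10</sub>/W<sub>10</sub>)] / [(Y<sub>01</sub>/W<sub>01</sub>)/(Y<sub>00</sub>/W<sub>00</sub>)] }, where W<sub>gt</sub> = Σ *e*<sub>it</sub> exp(γ*X*<sub>i</sub> + other covariate terms).

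With equal ratios W<sub>g1</sub> is the same multiple of W<sub>g0</sub> in both groups, and *X* cancels. With infants it does not:

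- One event in a 1-month baseline gives *X* = 1/(1/12) = 12 per person-year. One event in 3 years gives 1/3. The ratio is 36.
- The infant's follow-up-to-baseline ratio is 1/(1/12) = 12, against 1/3 for a full baseline.

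A few infants with large exp(γ*X*) can therefore dominate W<sub>g1</sub>, most easily in the smaller group of 400.

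**Simulation with a true effect.** 400 versus 8,000 children, true interaction log 0.8 = -0.223. Assumed: 4 events per year, gamma frailty variance 1, 30% infants, true baseline group difference 0.4 on the log scale.

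| Fit | Covariate scale | Minimum baseline | SD of interaction without term | SD with term |
|---|---|---|---|---|
| Random intercept | raw | 1 month | 0.063 | 0.063 |
| Independence GEE | raw | 1 month | 0.069 | 0.146 |
| Independence GEE | raw | 1 day | 0.060 | 0.379 |
| Independence GEE | log(rate + 0.5) | 1 month | 0.067 | 0.060 |

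In the random-intercept row the mean estimate is -0.228 without the term and -0.227 with it. With equal baselines the change is 0.000 in every replicate.

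What does move in the random-intercept model:

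- The group main effect falls from about 0.40 to 0.02-0.07. As rate ratios, exp(0.40) = 1.49 becomes exp(0.02) = 1.02 to exp(0.07) = 1.07.
- The random-intercept SD falls from about 1.16 to 0.61-0.67 (raw rate) or 0.08-0.22 (log rate).

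**Null simulations, independence GEE.** Assumed: frailty variance 1.5, pre/post correlation 0.6, 5% infants with 0.03-0.5 years of baseline, 15% aged 1-3, child-clustered standard errors, 200 replicates per run.

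- *1 event per year, raw rate:* four runs gave false-positive rates of 17%, 18%, 18.5% and 21.5%, against 5.5-6% without the term. The SD rose from 0.080-0.086 to 0.18-0.32, while the median standard error stayed at 0.087. The SD varies because a few replicates drive it; an interquartile-based SD in one run was 0.117.
- *4 per year, raw rate:* 5.5%, 6.5% and 7%.
- *8 per year, raw rate (one run):* 9.5%.
- *1% infants and 10% aged 1-3, raw rate:* 7.5%, 4.5% and 7.5% at 1, 4 and 8 per year.
- *Log rate:* 4.0-5.5% at 1, 4 and 8 per year.
- *Equal 3-year baselines:* SD identical with and without the term.

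Monte Carlo error at a true 5% is √(0.05×0.95/200) = 1.5 points. The 4-per-year results are therefore compatible with nominal error; the 1-per-year results are not.

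**The case against.** The strongest reply is that this is a wording slip with little consequence. The article names a mixed-effects model for this analysis, and in that model the interaction, which is the quantity of interest, is practically unchanged. Effectiveness is assessed in the post-period model, where baseline adjustment is right. Serious harm needs a population-averaged fit, an untransformed rate and very short baselines together, and the article fixes none of these three. One event per year is also hard to square with the combined outcome in a cohort selected for frequent use, although it is possible for a single component such as ED visits, and components are to be analysed separately.

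Most of this stands. A reader might infer that the covariate destabilises the interaction in general, or that the effectiveness result is unsafe. The documents support neither, for the reasons just given. Nor do they support cutting the covariates to a short list, since planned adjustment for condition severity has nothing to do with this defect. No evidence was found that bears on the time-series models.

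What remains is that the rule is stated, not merely left out, and it covers all regressions. An analysis plan that followed it would carry the error forward. GEE is named in the same paragraph, and matching on year of birth does not equalise baseline length among infants.

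**Conclusion.** Wrong as written; severity minor. The duplication follows from the text alone, and the exact cancellation under equal exposure ratios needs no assumed event rate or age mix.

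In the named mixed-effects model the cost is to interpretation. The group coefficient no longer describes the baseline difference between non-randomised groups, and between-child variation is understated. A reader could take the groups to be well balanced when they were not. Under a GEE fit with a raw rate and infants' short baselines, the interaction can be unstable and its standard error too small. Those magnitudes are illustrative: event rates, frailty, infant share and shortest baseline are all assumptions, because the article gives none of them.

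**What to change.** In Impact Evaluation Analyses, limit adjustment for the baseline service-use rate to the post-period model. State that the before/after interaction model omits it and uses log person-time in each period as an offset, so that short baselines enter as exposure. Keep every other planned covariate in both models, including condition type and severity. Possible wording: *The baseline service-use rate will be a covariate only in the model of intervention-period use; the before/after model will carry a log person-time offset and the remaining listed covariates.*

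The cost is one sentence. No data collection, matching or sample size changes.

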## Methodology

### Study design

The evaluation of RuralKidsGPS will consist of an integrated impact, implementation and economic evaluation embedded within a quasi-experimental study across four rural NSW local health districts (LHDs) in Southern, Northern and Western New South Wales and Murrumbidgee (Figure 1).

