### Recruitment

Children meeting the inclusion criteria for care coordination as described above will be recruited within each of the four LHDs. For children enrolled into the local service, the paediatric care coordinator (PCC) will discuss with each family their potential participation in the evaluation project. After providing a brief overview of the project, the PCC will ask permission for the contact details (parent name, contact number, email, and child name) to be shared with the researcher embedded with the local team. The embedded researcher will then contact the parent/carer and provide them with the participant information sheet and consent form.

Clinical staff (e.g. healthcare providers), and non-clinical staff (e.g. service managers) involved in the care coordination of the children will be recruited from each of the four LHDs and SCHN. Members of the research team will make direct contact with clinical and non-clinical staff and will provide them with an information sheet and consent form which describes what is involved in the research and that participation is voluntary. Upon agreement and consent, the implementation evaluation team will organise a suitable time to conduct the interview or focus group. Links to study surveys will be sent via an invitation email including the participant information form. These forms will also will be embedded in the electronic surveys and participants will be asked to confirm that they have read these and that they consent prior to completing the survey.

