**Figure 3 F3:**
[figure not shown]
Sources of data for linkage.

The comparison group will be identified using the linked administrative health data (ED presentations, hospital admissions, and OP appointments) and frequency matched with 20 children (to each case) by clinical diagnosis, year of birth, sex, local health district who and meet the eligibility criteria for health service use within the past 6 months (outlined in the Study Cohort section above) but who did not access RuralKidsGPS. A population-level evaluation will also be conducted which will include all CYP in the 4 health districts meeting the inclusion criteria.

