**Figure 4 F4:**
[figure not shown]
Using interrupted time series analysis to measure change before and after intervention. Adapted from Kontopantelis et al 2015 [13].

Regarding patient and family reported outcomes, we will describe them at each survey time point using mean and standard deviation, or median and inter-quartile range. We will conduct regression analysis of these outcomes at each survey (pre-intervention, 6-month and 12-month post-intervention), respectively, with intervention status as the main independent variable. We will control for participants’ socio-demographic, clinical and baseline outcome variables, and use the GEE approach to account for potential clustering effect by site. We will conduct intention-to-treat analysis.

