#### Implementation evaluation quantitative data collection

Data will be collected for each child before and after enrolment in the RuralKidsGPS care coordination model. In addition, key LHD staff involved in the delivery or management of RuralKidsGPS will be sent a link to a secure online survey, which includes the Acceptability, Appropriateness and Feasibility measure [15], Normalization Process Theory (NoMAD) tool [17] and Routinisation and Sustainability of work practices in long term care [18], at three time points: enrolment, 6 months and 12 months later as described in Table 3.

**Table 3 T3:** Quantitative data collection for children and families, clinician and non-clinicians at each of the four sites.

GROUP	INSTRUMENT	BASELINE (ENROLMENT)	6 MONTHS	12 MONTHS

Families	Paediatric Integrated Care Survey [6]	x	x	x

Clinician and non-clinicians	Intervention Acceptability, Appropriateness and Feasibility measure [15]	x	x	x

Clinicians and non-clinicians	NoMAD (Normalization Process Theory tool) [17]		x	x

Clinician and non-clinicians	Routinisation and sustainability of work practices in long term care [18]			x

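### GEE clustered on site has only four clusters: with the usual robust variance and normal reference, the health service use test would have about 17% to 24% type I error, not 5%

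*Protocol article*

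**What the plan says.** In Impact Evaluation Analyses, health service use in the 12 months after enrolment is compared between groups by Poisson or negative binomial regression. Clustering is handled as follows: "Considering potential clustering effect by site, we will use the generalised estimating equations (GEE) approach in the regression analysis". The same section later says of the patient and family reported outcomes that the analysis will "use the GEE approach to account for potential clustering effect by site".

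The number of clusters is not in doubt. Study design describes "a quasi-experimental study across four rural NSW local health districts (LHDs", Recruitment says "Children meeting the inclusion criteria for care coordination as described above will be recruited within each of the four LHDs", and the caption of Table 3 speaks of "Quantitative data collection for children and families, clinician and non-clinicians at each of the four sites". Site therefore means LHD, and there are four.

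On size and layout: "we aim to recruit 400 children across the four LHDs", and "We will match each case by 20 controls, resulting in a total of 8,000 controls". In Health Service Use, the comparison children are matched "by clinical diagnosis, year of birth, sex, local health district who and meet the eligibility criteria", so every LHD contains both groups. No variance estimator, small-sample correction, reference distribution or significance level is given.

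**The concern.** The GEE sandwich variance is justified as the number of independent clusters grows. With site as the cluster, the variance of the intervention effect rests on four residual sums, although there are 8,400 children. Adding controls does not help, because they enlarge the clusters without adding any. Two things then go wrong under the usual defaults: the estimated standard error is biased downward, and a normal reference ignores that the variance has only about 3 degrees of freedom.

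The main effectiveness comparison is at stake. A programme with no effect could be declared to reduce or increase health service use several times more often than the nominal level allows.

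**Working it through.** **Inputs from the article.** Four sites; 400 cases; 20 × 400 = 8,000 controls; both groups in each LHD; Poisson or negative binomial outcome; 90% power for a 20% difference.

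**Assumptions (not in the article).** Two-sided 5% level; mean of 1 or 4 events per child-year; negative binomial dispersion k of 1 or 2 (1.5 in a separate check); between-site SD of 0.2 on the log scale (0.3 in that check); 100 cases per site unless stated.

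**1. The plan's own figure.** The 90% power cannot be reproduced, because no event rate, dispersion or level is given. Ignoring clustering, Var(log RR) = (1/μ₁ + k)/400 + (1/μ₀ + k)/8,000 with μ₁ = 0.8 μ₀. The requirement is |ln 0.8| / SE = 0.2231 / SE = 1.96 + 1.28 = 3.24, so SE = 0.0688. That needs a comparison-group mean μ₀ of about 0.69 events per child-year if Poisson, 0.95 if k = 0.5, or 1.54 if k = 1.

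**2. Theory for four equal clusters.** The uncorrected sandwich statistic behaves like t on G − 1 = 3 df, with its SE shrunk by √((G − 1)/G) = √(3/4). The type I error is P(|t₃| > 1.96 × √0.75) = P(|t₃| > 1.697) = 18.8%. Removing only the SE bias leaves P(|t₃| > 1.96) = 14.5%. Most of the excess over 5% therefore comes from the normal reference, and the SE bias adds the step from 14.5% to 18.8%.

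**3. Simulation under no average effect.** 1:20 within each site, independence working correlation. There were 2,000 runs per row, except 600 for the covariate and LHD fixed-effect rows. The columns give rejection rates, then mean sandwich SE over true SD.

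| Setting | Site sandwich, normal | Site sandwich × G/(G−1), t₃ | Child-level robust, normal | SE / SD |
|---|---|---|---|---|
| Equal sites, mean 4, k = 1 | 18.6% | 4.8% | 4.2% | 0.81 |
| Equal sites, mean 1, k = 2 | 19.8% | 4.8% | 4.9% | 0.79 |
| Unequal sites, 160/120/80/40 cases | 21.2% | 5.5% | 5.5% | 0.75 |
| Five covariates | 17.3% | 4.5% | 4.5% | 0.84 |
| LHD fixed effects | 18.8% | 5.5% | 4.3% | 0.82 |
| Effect varies by LHD, SD 0.1 | 21.1% | 5.9% | 13.8% | 0.78 |
| Effect varies by LHD, SD 0.2 | 20.4% | 5.3% | 34.6% | 0.76 |
| 40 sites of 10 cases | 6.6% | 5.6% | 5.3% | 0.98 |

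An exchangeable GEE fitted with standard software (ratio 1:5, 400 runs) rejected 24%, with a Monte Carlo error of about 2 points. The 40-site row shows that the small number of clusters is the cause. The fixed-effect row shows that adding LHD indicators does not help while the sandwich is still formed by site; the level at which the SE is formed must change too.

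**4. Effect varying by LHD.** Take μ = 4 and, under no average effect, a child-level SE of √[(1/μ + k)(1/400 + 1/8,000)]. The estimate's true SD, seen as an average beyond these LHDs, is √(SE² + τ²/4), where τ is the SD of the effect across LHDs.
- k = 1.5: SE = 0.0678. For τ = 0.1 the SD is 0.0842, and rejection is P(|Z| > 1.96 × 0.0678/0.0842) = 11.5%. For τ = 0.2 the SD is 0.1208, giving 27%.
- k = 1: SE = 0.0573, giving 14% and 33%.

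This brackets the rounded 12% to 30% used here.

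**5. Price of correcting the site-clustered test.** The intervals widen by 3.18 × √(4/3) / 1.96 = 1.87. A test with 90% power under a normal reference (noncentrality 3.24) keeps about 59% with t on 3 df.

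**The case against.** The strongest reply is that the article names GEE and the cluster unit but no variance estimator, correction or reference distribution, and an analysis plan that is not shown may supply them. The result does depend on them: in one null setting (mean 4, dispersion 1.5, site SD 0.3) the uncorrected sandwich rejected 19.4%, the corrected version with t on 3 df 5.6%, and a scaled model-based SE under independence 4.7%. This stands. A reader might infer that the planned test has about 20% error as a fact; the documents support that only for the uncorrected default. What the article does fix is GEE with four clusters, so the plan faces either inflated error or, once corrected, a loss of power that its 90% figure does not mention.

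A reader might also infer that the error rate applies to every regression outcome. It does not. The section on patient and family reported outcomes collects those measures only in the intervention cohort, so their contrast by intervention status cannot be estimated; that is a separate matter. Nor do the calculations cover the mixed-effect before/after model or the interrupted time series.

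Finally, one might conclude that LHD is merely a stratum and site clustering can be deleted. The article does not support this either: a local coordinator role delivers the programme in each LHD, and local differences in resources, staff and management support are expected. The effect may well differ by LHD, and child-level errors would then be too small for any inference beyond these four.

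**Conclusion.** The concern holds in a conditional form. Four sites are too few for the usual GEE robust variance. With an uncorrected sandwich and a normal reference at an assumed two-sided 5% level, the type I error for the health service use comparison is about 17% to 24%, and the standard error is about 16% to 25% too small. Having both groups in every LHD does not remove the problem, since the simulations used that layout; nor does covariate adjustment. The result changed little over the assumed means, dispersions and site sizes.

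**What to change.** For the health service use comparison:

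- Main analysis: enter LHD as a fixed effect (three indicators), with robust standard errors at child or matched-set level. State that inference is for these four LHDs, and report LHD-specific effects.
- Sensitivity analysis: keep a site-clustered analysis, with a named small-sample variance correction such as G/(G − 1) and a t reference on 3 df. It held about 5% to 6% in the runs above, and up to about 8% in a further check. It is the guard against an effect that varies by LHD.
- State the significance level, the variance estimator and the reference distribution, and say whether the GEE sentence also governs the mixed-effect interaction model.

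The cost is wording only, with no new data, and it can be settled before the linked data are analysed. The downsides are real: the main inference is limited to the four LHDs, and the corrected site-clustered intervals are about 1.9 times as wide as the uncorrected ones, so the sensitivity analysis will have much less than 90% power.

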Additionally, we will plot monthly rate of health service use for both intervention and comparison groups over baseline and intervention periods. We will undertake an interrupted time series (ITS) analysis to gain a better understanding of how the effect of intervention changes over time (e.g. to identify when the intervention starts to take effect). ITS is one of the most effective quasi-experimental evaluation methods and has been used in many health intervention evaluations [13]. An ITS analysis allows us to control for time-varying confounders such as seasonality and co-occurring competing interventions, thereby addressing important threats to internal validity and causal inference. Figure 4 illustrates using ITS to measure change before and after intervention.

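### The interrupted time series is credited with controlling for co-occurring interventions, and the end of its pre-trend is raised by the six-month selection rule; no between-group contrast or comparison index date is stated

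*Protocol article*

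**What the plan says.** The Impact Evaluation Analyses section adds an ITS to the regression models. Its stated purpose is "to identify when the intervention starts to take effect", and its stated strength is that "An ITS analysis allows us to control for time-varying confounders such as seasonality and co-occurring competing interventions". The sentence carries no qualification.

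The same section says "we will plot monthly rate of health service use for both intervention and comparison groups over baseline and intervention periods". Rates are calculated "during the baseline (3 years prior to enrolment) and the intervention period (12 months after enrolment), respectively", which gives 36 monthly points before enrolment and 12 after. The contrast attached to the ITS is before versus after: "Figure 4 illustrates using ITS to measure change before and after intervention". No group-by-level or group-by-slope term is given for it.

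Under Study cohort, children aged 6 months or more qualify through "frequent use of health services within the last six-month period": two or more emergency department (ED) presentations, an admission of seven days or more, or two or more outpatient appointments. These are the service types that make up the primary outcome.

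The paragraph on the comparison group (under Health Service Use, after Figure 3) requires comparison children to "meet the eligibility criteria for health service use within the past 6 months". It does not say from which date those six months are counted.

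**The concern.** There are two problems.

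1. **What the ITS can control.** A segmented model on one series attributes to the programme whatever else changes at the interruption. A concurrent comparison series helps only where the other change reaches both groups equally. The protocol claims more than the method delivers.

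2. **What the pre-trend contains.** Children enter because their recent use was high. On average use then returns to its usual level, with or without the programme. If the six qualifying months stay in the pre-trend, the fitted line tilts upwards and is projected above the usual level. The ordinary return then appears as a drop exactly at enrolment.

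The ITS is there to date the onset of effect. An artefact located at enrolment would suggest an immediate onset. Its possible size matters because the study is planned around a 20% difference between groups and a 20% within-group decrease.

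**Working it through.** The protocol states no figure for the ITS, so there is none to reproduce. The check asks what the described series would show if the programme did nothing.

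**Inputs from the protocol:** 36 pre-enrolment and 12 post-enrolment months; selection on two or more ED or two or more outpatient contacts in the last six months; no months excluded.

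**Inputs assumed, because the protocol gives none:** population rates of 1–2 ED and 2–12 outpatient contacts per year; gamma variance between children of 0.5, 1 or 2; with or without monthly fluctuation (autocorrelation 0.8, log-SD 0.7). The seven-day admission route was not simulated.

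**Step 1: hand calculation.** Let yearly use be *a* in the first 30 months and *b* in the last six. For a straight line through 36 points:

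- mean = a + (6/36)(b − a)
- sum of squares of time = 36 × (36² − 1)/12 = 3,885
- slope = (b − a) × 6 × (33.5 − 18.5)/3,885 = 0.02317(b − a) per month
- projection to month 37 = a + (b − a)(0.1667 + 0.02317 × 18.5) = a + 0.595(b − a)

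*Strong selection* (ED 1/yr, outpatient 2/yr, variance 0.5). Simulated use was 4.59 in the first 30 months, 6.76 in the last six and 4.59 after enrolment. The projection is 4.59 + 0.595 × 2.17 = 5.88, and 4.59/5.88 = 0.78, a false step of about -22%. The segmented Poisson fit gave -23%. The plain pre-period mean is (30 × 4.59 + 6 × 6.76)/36 = 4.95, and 4.59/4.95 = 0.93, a fall of only 7%. Fitting a trend through the qualifying months roughly triples the artefact.

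*Weak selection* (ED 2/yr, outpatient 12/yr, variance 1). Use was 17.91, 18.49 and 17.90. The projection is 17.91 + 0.595 × 0.58 = 18.26, and 17.90/18.26 = 0.98, a false step of -2%. The simulation also gave -2%.

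**Step 2: range over all assumed scenarios, uncontrolled series, no true effect.**

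| Outcome | False step at enrolment |
|---|---|
| Total use | -1% to -24% |
| ED | -1% to -20% |
| Outpatient | -1% to -25% |
| Total use, six months omitted | -1% to +3% |

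**Step 3: controlled series.** Both groups meet the same use criterion, and the figures are differences between groups in the false step.

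| Rates (ED, outpatient per year); variance 1 | Aligned index date | Referral weighted by recent use | Comparison index 6 months earlier |
|---|---|---|---|
| 1, 4; no fluctuation | 0.2% | -3.0% | -2.3% |
| 1, 4; fluctuation | 0.6% | -5.4% | +3.5% |
| 2, 6; fluctuation | 0.1% | -4.3% | +2.5% |

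A further set of zero-effect runs let referral favour recent heavy users and measured the 12-month average against comparison children who only met the threshold. The false difference was -2.5% to -20%. Omitting the six months reduced it to about 0% to -9%.

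**Step 4: co-occurring intervention.** Suppose something else multiplies use by 0.85 from enrolment. A single series shows a step of 0.85, that is -15%. A controlled series shows 0.85/0.85 = 1 if both groups receive it, and 0.85/1 = 0.85, again -15%, if only the intervention group does.

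**The case against.** The strongest reply is that the ITS may well be meant as a comparative analysis. The Health Service Use section compares change and trend with a matched group, the mixed-effects model contains a group-by-time interaction, and the sentence just before the ITS plots both groups. The before/after wording belongs to an adapted figure that is not shown, and a condensed article may leave model terms to a fuller plan. Comparison children meet the same use criterion, so both series would carry the pre-enrolment peak and a contrast between them would largely remove it. Much of this stands, and it is why the fall is stated here only for an uncontrolled fit. It does not rescue the sentence on co-occurring interventions, which is an affirmative claim and too broad. The interaction term belongs to a different, two-period model. The peak cancels only if index dates line up, and none is given for comparison children. Referral also selects in the intervention group alone.

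The size is also open to challenge. Children with medical complexity may attend outpatients so often that two visits in six months hardly select, and the artefact is then small. Children under 6 months are exempt from the rule. A delay between referral and enrolment would move the qualifying window, and a calendar-time axis would blur the peak. These caveats hold. The protocol does, however, define the periods by enrolment, so enrolment-centred time is the natural reading.

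Omitting six months might look superfluous once the series is controlled. It is not if referral depends on recent use, as the last runs in the working show.

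**Conclusion.** The point holds in a limited form. The claim about co-occurring interventions is wrong as worded. The six qualifying months lie at the end of the pre-trend, and nothing in the protocol excludes or models them. With no true effect, an uncontrolled segmented fit gives a false step of roughly -1% to -25%. That range rests on assumed rates and dispersion, on selection in the six months directly before enrolment, and on children old enough for the rule to apply. A controlled ITS with the same criterion and aligned index dates brings the difference to under 1%, unless referral favours recent heavy users.

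A reader might infer that the ITS is bound to show a large immediate effect even for an inert programme. The protocol does not support that: the size depends on figures it does not give, and the comparison group is a real, if incompletely specified, safeguard. A reader might also infer that the main effectiveness result is biased in the same way. This point does not show that. The primary analysis is a between-group regression of use after enrolment and fits no pre-trend. What is affected is the supporting ITS on when an effect begins.

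**What to change.** 1. Specify a controlled ITS with group-by-level and group-by-slope terms as the estimates of interest.
2. Give each comparison child an index date aligned with the enrolment of the matched case, and match or adjust for use in the six months before it.
3. Omit months -6 to -1 from the pre-trend in both groups, or model them separately.
4. Limit the sentence on confounding: the controlled series removes only changes that affect both groups equally, and an intervention that starts at the same time in the intervention group alone cannot be separated from the programme.

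The cost is wording and modest programming on data already requested. If the six months are omitted, the pre-trend rests on 36 − 6 = 30 months, so it is somewhat less precise.
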